## 6.4 Exclusion criteria

1. More than 4 hours from hospital admission to randomization
2. Suspected infection or sepsis
3. Known severe COPD
4. Systolic blood pressure <90 mmHg

## 6.5 Estimated Study start and duration

We expect inclusion to begin in March 2024. Inclusion is planned to be completed after 1 year. The trial is terminated after the last patient has been assessed for 30-days. Since biochemical analyses of the research biobank samples for some of the secondary endpoints, not part of the main trial publications is expected to be performed after 30-day follow-up, the trial database and research biobank will exist in a non-anonymized format for up to 10 years following inclusion and follow-up of the last patient.

# 7. Outcomes

## 7.1 Primary outcome

## Pulmonary parenchymal fluid content measured by ReDS after 24 hours preceded by 10 minutes without oxygen-supplementation.

## 7.2 Secondary outcomes

1. Arterial blood gas concentration after 24 hours preceded by 10 minutes without oxygen-supplementation.
2. All-cause mortality at day 30
3. Days alive out-of-hospital to day 30
4. Time to freedom from oxygen-supplementation

## 7.3 Eksploratory outcomes

1. Change from baseline in log-transformed biomarkers (N-Terminal Pro-Brain Natriuretic Peptide (NTproBNP), troponin T, creatinine, neuron-specific enolase, procalcitonin) to 24 hours from admission.
2. 2D and 3D systolic and diastolic strain parameters (i.e. time to peak strain, systolic and diastolic strain rates, displacements, velocities, torsion) and traditional TTE measures as well such as ventricular volumetry and function, stroke volume derived from the velocity time integral of the left ventricular outflow tract, tissue doppler and mitral valve inflow patterns to assess diastolic function, right ventricular fractional area change and tricuspid annular plane systolic excursion.
3. Days alive out-of-ICU until day 30
4. Patient-reported dyspnea on a VAS-scale 1-100 after 24 hours
5. Number of patients where intervention is terminated (opt out) before 6 hours
6. Time within targeted SpO2-interval (89-91 % in restrictive group, 95-97% in liberal group)
7. Multiple B-lines in at least two areas on lung ultrasound identifying interstitial syndrome (yes/no).
8. FiO2, Blood pressure, respiratory rate, heart rate after 24 hours
9. Quality of life and depression: HADS, SF-36 and EQ-5D-5L

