# 5. Intervention

Random allocation to 1 of 2 strategies:

- Liberal oxygenation group = SpO2 target of 96%.
- Restrictive oxygenation group = SpO2 target of 90%.

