5.1 Detailed intervention and suggested initial treatment

Immediately after admission, the standard of care-treatment can be initiated as per discretion of the treating physician. Oxygen can be administered freely. The attending physician at the site will assess the patient’s eligibility for inclusion in the trial. After successful screening, the patient will be asked for written informed consent from study investigators. The sites will aim to obtain the consents as soon as possible. Patients will have nasal cannula or oxygen mask placed as the usual standard of care.

Patients will be screened and randomized in the emergency department to either liberal or restrictive oxygenation after providing informed written consent and oxygen is titrated to the prespecified target range using an automated feedback device (O2MATIC). Consented patients will be randomly allocated to study groups via the web-based system within REDCap. The allocation will be concealed. Time at randomization will be considered as study time zero (T0). All patients will receive usual standard of care except for their O2 management. The intervention will last for 24 h. After 24 h, patients will be switched over to usual care for oxygen therapy. We selected the 24 h time frame because in previous studies most patients with AHF were no longer on oxygen after 24 h [27]. If the treating physician thinks, that the patient need another oxygenation target and it is thought to be harmful to continue with the allocated target, the intervention-phase can be stopped prematurely.

Blinding

The intervention will be administrated double-blinded using the O2MATIC-device, which will titrate the oxygen-supplementation towards the intended target SpO2 without it being visible for patients, investigators or treating personnel. The robot will be programmed to deliver the intervention, record minute-by-minute data of oxygen-supplementation and SpO2. Furthermore, the robot will give an alarm if SpO2 drops below 88%. During the intervention-phase, SpO2 will not be measured by the nurses.

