## 6.3 Inclusion criteria

1. Age ≥ 18 years
2. Acute (within minutes to days) onset or worsening of subjective dyspnea
3. Oxygen saturation <92% or need of oxygen
4. At least one of the following (clinical or radiological signs of congestion):
   1. Pulmonary rales
   2. Chest X-ray or CT with pulmonary congestion
   3. Lung ultrasound with multiple B-lines

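### Time in target counts minutes on zero oxygen flow above the band as out of target, so it tends to understate delivery of the strategy, mainly in the restrictive arm

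*Protocol*

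**What the plan says.** Section 5 of the Protocol sets the two strategies as "Restrictive oxygenation group = SpO2 target of 90"% and "Liberal oxygenation group = SpO2 target of 96"%. Section 5.1 gives the task to an automated device, "which will titrate the oxygen-supplementation towards the intended target SpO2", and adds that "The intervention will last for 24 h". The device will "record minute-by-minute data of oxygen-supplementation and SpO2".

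Section 7.3, item 6, turns this into an exploratory outcome: "Time within targeted SpO2-interval (89-91 % in restrictive group, 95-97% in liberal group"). Each band is the target plus or minus one point. Minutes without supplemental oxygen get no separate treatment, and the item does not say whether the result is hours or a percentage, or what the denominator is.

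Three other places bear on how often patients will be without oxygen during the intervention:

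- Section 5.1 justifies the length of the intervention by previous studies in which "most patients with AHF were no longer on oxygen after 24 h".
- Section 7.2 lists the time until the patient is free of oxygen as a secondary outcome.
- Section 6.3 admits patients with "Oxygen saturation <92% or need of oxygen", so a patient already on oxygen can enter with no stated room-air value.

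**The concern.** The upper limit of a saturation band can be enforced only while there is oxygen to withdraw. At zero flow the device has done all it can. A restrictive-arm patient at 94% on room air is receiving what the strategy asks for, which is no oxygen, but every such minute lies outside 89-91%. In the liberal arm the same patient would be given oxygen towards 96%, and those minutes could count as in target.

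Two different situations therefore get the same score in the restrictive arm: saturation above 91% because the patient has recovered, and saturation above 91% because oxygen is still running when it should have been reduced. Only the second is a shortfall in delivery.

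Item 6 is the only listed outcome that follows saturation against target over the whole intervention, so readers will use it to judge whether the strategies were delivered. If restrictive patients recover faster, as the trial's hypothesis would suggest, their time in target falls. A low value in that arm could be misread as poor delivery, and a neutral primary result could be put down to it.

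**Working it through.** **The plan's own figures.** The Protocol states no expected time in target, so there is nothing to reproduce for item 6. The one design figure that can be checked is the sample size: 2 × (1.960 + 1.282)² × 6.8² / 4² = 60.7, hence 61 per arm and 122 in total, as stated in section 8. The saturation bands do not enter it.

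**Which minutes are affected**

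| Situation | Strategy followed? | Item 6 as written |
| --- | --- | --- |
| Restrictive, 94%, zero flow | yes | out of target |
| Restrictive, 94%, oxygen running | no | out of target |
| Liberal, 96%, zero flow | yes | in target |
| Liberal, 98%, zero flow | yes | out of target |

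The first two rows cannot be told apart. The last row shows that the liberal arm is exposed too, but only above 97%.

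**Ceiling for one patient.** Assume a 24 h denominator and h hours on room air above 91%. With perfect control otherwise, the maximum score is (24 − h)/24:

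- h = 6: 18/24 = 75%
- h = 12: 12/24 = 50%
- h = 18: 6/24 = 25%

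The values of h are assumptions. The Protocol gives none.

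**With imperfect control.** Let f be the share of time on room air above 91% and q the share of the remaining minutes in band. The score as written is q(1 − f). If the zero-flow minutes above range are credited, it is q(1 − f) + f. With q = 0.90 (assumed):

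| f | As written | Credited |
| --- | --- | --- |
| 0.10 | 81% | 91% |
| 0.25 | 67.5% | 92.5% |
| 0.50 | 45% | 95% |
| 0.75 | 22.5% | 97.5% |

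**Both arms under the same device performance.** Assume room-air saturation over the patient-minutes is normal with SD 2 to 3 points, and write F for its cumulative distribution. Saturation is read in whole points, so the band edges are 88.5, 91.5, 94.5 and 97.5. A minute already in band on room air counts fully. A minute below the band is brought into it with probability 0.90. Then:

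- restrictive = 0.90 × F(88.5) + [F(91.5) − F(88.5)]
- liberal = 0.90 × F(94.5) + [F(97.5) − F(94.5)]

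For mean 92 and SD 2, F at the four edges is 0.040, 0.401, 0.894 and 0.997. Restrictive is 0.036 + 0.361 = 39.7%. Liberal is 0.805 + 0.103 = 90.8%.

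| Mean room-air SpO2 | Minutes above 91% | Minutes above 97% | Restrictive, as written | Liberal, as written |
| --- | --- | --- | --- | --- |
| 90% | 23-31% | 0-0.6% | 66-75% | 90% |
| 92% | 57-60% | 0.3-3% | 40-42% | 89-91% |
| 94% | 80-89% | 4-12% | 10.5-20% | 82-90% |

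The device works equally well in both columns. The gap comes from where the upper limits lie relative to room-air saturation. The figures depend on the assumed distribution. The direction does not, as long as more room-air minutes lie above 91% than above 97%.

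**The case against.** The strongest reply is that item 6 is a correct description of exposure. A restrictive patient at 94% on room air was not near 90%. If many patients were like that, the arms differed less in saturation than intended, and this could truly contribute to a neutral result. Crediting those minutes answers another question, whether the strategy was followed, and could hide poor separation. This stands, and it is why time in band should be kept and not replaced.

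Several stronger readings that a reader might infer do not hold:

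- *That this is the plan's only check on delivery.* Section 7.3 also lists termination of the intervention before 6 hours and FiO2 at 24 hours, and the secondary outcome on time until free of oxygen would show weaning directly. Item 6 is unique only in following saturation against target throughout.
- *That the plan classes these minutes as failures.* It does not use the word, sets no adherence threshold and defines no per-protocol set from item 6.
- *That only one arm is affected.* The liberal arm loses zero-flow minutes above 97%.
- *That the Protocol predicts many hours off oxygen.* Its remark rests on previous studies and does not say how early in the 24 h patients came off.

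It can also be said that denominators and the handling of zero-flow minutes belong in a statistical analysis plan, which is not at hand. That would answer a complaint about missing detail. Here, however, the Protocol fixes numerical bands with an upper limit, and those bands themselves produce the asymmetric reading.

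**Conclusion.** The point holds in a limited form. As defined, time in target puts minutes at zero flow above the upper limit out of target although the strategy is being followed. This is to be expected mainly in the restrictive arm, so the measure would tend to understate delivery there, and it does not separate recovery from over-oxygenation.

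That such minutes will occur follows from the Protocol's own expectation about weaning. How many is unknown. The ceilings of 75%, 50% and 25% rest on a 24 h denominator and on assumed room-air times of 6, 12 and 18 h, and the comparison between arms rests on an assumed distribution of room-air saturation. Neither is a forecast.

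It would be wrong to infer that the trial's main conclusion is at risk. The outcome is exploratory, analyses are by modified intention to treat, and the primary analysis and the 122 patients are untouched. What is at stake is how delivery and separation between the arms will be read. The change is worth making before the data are analysed.

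**What to change.** Keep time in band and label it a description of saturation exposure. From the device log, by the same rule in both arms, report time:

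1. below range;
2. in range;
3. above range with oxygen running;
4. above range at zero flow.

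Define delivery as allocated as 2 plus 4, and state the denominator, including for patients whose intervention is stopped early. Show mean SpO2 and mean oxygen flow by arm as the measure of separation.

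The four parts should always be shown with the sum. The credited score also rises with recovery (91% at f = 0.10 and 97.5% at f = 0.75 in the table above, with control unchanged), so the sum alone could flatter the arm that weans sooner.

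The cost is one more derived variable and a few lines of code, since flow and saturation are already logged each minute. The saturation targets and clinical management stay as they are.

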# 8. Sample size calculations and statistical analysis plan

In a validation-trial of ReDS, Amir et al investigated 16 patients with acute heart failure and found a mean fluid content of 39.8 + 6.8 % [25]. Similar results were seen when estimating fluid content by the chest CT, which is regarded as the gold standard.

To have 90 % power to find a difference of 4 % in lung fluid content (change from 39.8% to 35.8%) with a standard deviation of 6.8, we need to include 122 patients (61 in each group). The α-level is 0.05, and the beta is 10%. We expect minimal dropouts. The study will include patients over an estimated period of 1 years in two centers. We will include patients until we have reached the estimated sample size without any missing values in the primary outcome, to ensure that we can conclude on our primary hypothesis.

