# 12. Statistical analyses plan

Baseline characteristics and outcomes of the patients in the groups will be compared individually. The primary exposure variable is allocation to the intervention group compared to control group. Categorical variables will be presented as numbers (frequencies) and compared with the Chi-Squared or the Fisher’s exact test, as appropriate, whereas continuous variables will be presented as mean ±SD if normally distributed, and as median (25^th^ percentile-75^th^ percentile) if non-normally distributed and compared with the T-test. In continues data, there are non-normally distributed, logarithmic transformation will be applied to approximate normal distribution as appropriate. Repeated measurements, mixed models will be made for analysis of the continuous variables with multiple measurements.

Missing data

In case of missingness greater than 5% for the primary endpoint, multiple imputations by chained equations will be applied as sensitivity analysis with generation of 10 individual data sets.

For other endpoints, first a worst case and best-case analysis will be made and if significant differences, multiple imputations will be performed.

Analysis of survival data and other outcomes

Kaplan-Meier curves for each group will be graphically displayed and compared by the log-rank test. Further multivariable Cox proportional hazard models will be applied to assess differences in time to death between treatment groups. These models will sequentially be adjusted for the interaction between treatment allocation, and each of the predefined covariates. Further, models stratified by individual components of the predefined covariates will be made as hypothesis generating. Any changes from the pre-specified analysis plan will be reported.

Outcomes will be evaluated using univariable and multivariable logistic regression models after examining assumptions of linearity and proportionality. Hazard ratios (HRs) and Odds ratios (ORs) with corresponding two-sided 95% confidence intervals (CI) will be presented.

Multivariable models are adjusted for:

*Admission SBP (quartiles), age, sex, body mass index, LVEF at admission (>50, 40-50, <40), NT-proBNP (above/below median), eGFR, supraventricular arrhythmia at admission, comorbidities (history of heart failure, obstructive pulmonary disease), systemic congested (Yes/no, defined as at least 3 kg above ideal weight at admission).*

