# Appendix 4: study-related procedures

| Time | **Screening, baseline pre-randomization assessment** | **Randomization** | **12 h post randomization** | **24 h post randomization** | **Discharge** |
| --- | --- | --- | --- | --- | --- |
| Informed consent, patient | x |  |  |  |  |
| Demographics | x |  |  |  |  |
| Inclusion/ exclusion criteria | x |  |  |  |  |
| Medical history | x |  |  |  |  |
| Concomitant medications | x |  |  | x | x |
| Routine blood test | x |  |  | x (morning) |  |
| Arterial blood gas | x |  | x | x |  |
| ECG | x |  |  | x |  |
| Vital signs | x |  | x | x |  |
| Chest x-ray | x |  |  |  |  |
| Echocardiography | x |  |  | x |  |
| Focus lung-ultrasound | X |  |  | x |  |
| ReDS | X |  |  | X |  |
| Patient-dyspnea | X |  |  | X |  |
| Plasma volume | X |  |  | X |  |
| 5Q-DL |  |  |  |  | x |
| Adverse events reporting |  |  |  |  | x |

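### Exploratory item 7 cuts lung ultrasound to yes/no at two areas and leaves the baseline scan out; a graded, baseline-adjusted count would compare the arms better at small cost

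*Protocol*

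**What the plan says.** Section 7.3 lists nine exploratory outcomes. Item 7 is "Multiple B-lines in at least two areas on lung ultrasound identifying interstitial syndrome (yes/no". It names no time point, but Appendix 4 schedules "Focus lung-ultrasound" before randomization and again at 24 h, so I read it as a 24 h outcome.

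Section 12 (Statistical analyses plan) says "Categorical variables will be presented as numbers (frequencies) and compared with the Chi-Squared or the Fisher’s exact test, as appropriate", and it also foresees univariable and multivariable logistic regression. The covariates listed for the multivariable models do not include the baseline ultrasound finding.

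Section 6.3 requires "At least one of the following (clinical or radiological signs of congestion". The three alternatives are pulmonary rales, congestion on chest X-ray or CT, and "Lung ultrasound with multiple B-lines". The entry wording has no two-area threshold.

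The primary outcome in section 7.1 is "Pulmonary parenchymal fluid content measured by ReDS after 24 hours preceded by 10 minutes without oxygen-supplementation", kept as a percentage. Section 8 plans for a "difference of 4 % in lung fluid content (change from 39.8% to 35.8%) with a standard deviation of 6.8". It makes no power statement for item 7.

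**The concern.** The two-area rule answers a diagnostic question: does this patient have interstitial syndrome? The trial asks a different one, namely how much congestion differs between the arms after 24 h. Under the rule, a fall from, say, six positive areas to two is no change, while a fall from two to one is a full response. The protocol handles other graded measures differently: ReDS stays a percentage, and dyspnoea (item 4) is measured on a visual analogue scale.

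Lung ultrasound is the only other listed outcome that looks directly at lung congestion. Chest X-ray is scheduled at baseline only, and the echocardiographic outcomes are cardiac. Item 7 is thus a natural companion to the ReDS result, and the yes/no definition makes it a less sensitive one. What is at stake is precision in an exploratory outcome, not the trial's main conclusion.

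**Working it through.** **Inputs from the protocol.** Difference 4, SD 6.8, 61 per arm, power 90% (section 8); two-sided 0.05 and a chi-squared or Fisher test for categorical data (section 12).

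**Assumptions of this check.**
- The ultrasound burden behaves like a normal latent score with the primary's standardised effect.
- A share p_L of the liberal arm is positive at 24 h. The protocol gives no value, so a range is used.
- For the graded analysis, the number of positive areas runs from 0 to 8. The protocol names no zone scheme.

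**Step 1: the plan's own figure.** d = 4/6.8 = 0.588. Per arm, n = 2 × (1.960 + 1.282)² / 0.588² = 60.7, rounded up to 61, or 122 in total. This matches section 8. At 61 per arm, power on the full scale is 90.1% (normal) or 89.7% (t-test).

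**Step 2: the yes/no cut.** Restrictive-arm positivity is p_R = Φ(z(p_L) − d). For p_L = 0.80, p_R = Φ(0.842 − 0.588) = 0.600. With pooled proportion 0.70:
- null standard error: √(2 × 0.70 × 0.30 / 61) = 0.0830
- alternative standard error: √((0.80 × 0.20 + 0.60 × 0.40) / 61) = 0.0810
- power: Φ((0.200 − 1.960 × 0.0830) / 0.0810) = Φ(0.46) = 68%

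Exact enumeration of the uncorrected chi-squared test also gives 68%.

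**Step 3: the graded alternative.** The same latent score was grouped into 0 to 8 areas, with steps of 0.3 and 0.5 SD and the two-area boundary at the same point. The arms were compared by a Mann-Whitney test over 4,000 simulated trials per setting.

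| Positive at 24 h, liberal | Positive at 24 h, restrictive | Power, yes/no (chi-squared) | Power, rank test on 0–8 count |
| --- | --- | --- | --- |
| 60% | 37% | 75% | about 84–86% |
| 76% | 55% | 70% | about 87% |
| 80% | 60% | 68% | about 86–87% |
| 90% | 76% | 56% | about 87–88% |

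The gap is roughly 10 points at 60% positive, 17 at 76%, 18 to 19 at 80% and 31 at 90%. Fisher's exact test, which section 12 also allows, has lower power: 61% at 80% positive and 47% at 90%.

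**Step 4: a reference point within the range.** The background section gives 35% as the upper normal limit for ReDS. If the ultrasound cut sat at the equivalent point (a further assumption), positivity would be Φ((39.8 − 35)/6.8) = 76% in the liberal arm and Φ((35.8 − 35)/6.8) = 55% in the restrictive arm. That is the 76% row.

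**Step 5: logistic regression.** It models the same yes/no variable. Covariates can sharpen the comparison, but cannot tell a patient with two positive areas from one with six, so what the cut discards is not recovered.

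**The case against.** The case on the other side has weight. Item 7 is one of nine exploratory outcomes in a self-described pilot trial, and the protocol promises no power for it. Interstitial syndrome yes/no is easy to read clinically, and an analysis plan that is not shown might add a count. All this bears on importance. It does not change the definition that section 7.3 fixes, and a count that is not recorded during the scan may not be recoverable later.

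Three stronger readings are tempting, and the documents do not support them.

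- **That a full count is already being made.** No zone scheme or scoring sheet is described, and an operator can satisfy the two-area rule by stopping at the second positive area. A graded outcome is therefore some extra work.
- **That most patients start and stay positive because B-lines are an entry sign.** They are one of three alternatives, without the two-area threshold, and no 24 h rate is given. Any ceiling is conditional. Assuming 95% positivity would bring yes/no power down to 44%, but nothing in the protocol points to that rate.
- **That a null result on item 7 would look like a contradiction of ReDS.** Section 12 calls for odds ratios with 95% confidence intervals, so imprecision would be visible. NT-proBNP, dyspnoea, echocardiography and blood gases also bear on the question, though less directly.

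The size of the loss also depends on borrowing the ReDS effect for ultrasound, which the protocol neither states nor supports. The loss of information itself stands.

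**Conclusion.** The point holds as a modest improvement to an exploratory outcome. The yes/no definition discards the degree of change and does not use the baseline scan. With the primary's standardised effect and 61 per arm, it would lower power from about 84–88% for a graded rank comparison to between 75% and 56% as liberal-arm positivity goes from 60% to 90%. These figures are for unadjusted comparisons and are only as good as the assumed effect, zone count and positivity rates. The direction does not depend on the exact rate: the yes/no comparison had the lower power at every rate tried. The primary outcome, the secondary outcomes and the sample size are untouched.

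**What to change.** Redefine item 7 as the number of B-line-positive areas at 24 h, over a fixed set of zones used at both sites. Compare the arms with the baseline number as covariate, by proportional-odds regression or rank-based ANCOVA. Report interstitial syndrome yes/no as a descriptive summary.

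The cost is a revised sentence in section 7.3, a short common zone scheme with a rule for zones that cannot be scanned, and a data field for the number of positive areas at each of the two scans. Operators must scan and record every zone rather than stop at two positive ones. The effect is then reported as a shift in areas, which is less familiar than a difference in proportions. No additional scan or patient is needed. The change should be made before further scans are recorded as yes/no only.
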